### Secondary objectives

The key secondary objective of this study is to establish a proof of concept for the FutureU for Mental Health intervention. This will be established by (a) demonstration that the intervention has the intended effect on the targeted cognitive mechanisms (i.e. enhancement of the quality of mental imagery), and (b) evidence of improvement in clinical outcomes or reduction of negative affect versus the control group, both immediately following the intervention, and 1 week and 3 months post intervention.

Another secondary objective of this study is to assess whether the virtual reality intervention is strong for those participants who experience deficits in executive functioning.

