### Research hypotheses

We expect the FutureU for Mental Health intervention to be broadly accepted and feasible to implement. We expect participants to feel embodied and engaged with the virtual environment and intervention exercises.

We hypothesize that the FutureU for Mental Health (FutureU-MH) virtual reality intervention (Coping Plan plus Self-Help and Positive Future Memories interventions, collectively) will reduce negative affect, depressive symptoms, and severity/frequency of suicidal ideation, and improve mood by enhancing the quality of mental imagery in thoughts of the future and of the future self. We hypothesize this effect will continue to grow over time as participants practice a new way of thinking and cognitive patterns gradually change. Specifically, participants who receive the Coping Plan intervention plus FutureU-MH (TX: the treatment group) are expected to see an improvement in the quality of mental imagery in thoughts of the future (vividness) and of the future self (vividness, valence, connectedness, and similarity), while no change in quality of thoughts is expected for participants who receive only treatment as usual, the coping plan intervention (TAU: the control group). In turn, we expect that participants receiving TX will subsequently show a greater reduction in negative affect, depressive symptoms, and severity/frequency of suicidal ideation and a greater improvement in mood than participants receiving TAU. Similarly, participants receiving TX are expected to see an improvement in the quality of mental imagery in thoughts of the future and of the future self, while no change in quality of thoughts is expected for participants receiving TAU. These effects will be strongest at the 1-week and 3-month follow-ups.

Finally, in a more highly powered study, we hypothesize that this intervention would be most effective for individuals experiencing executive dysfunction as the images and structure provided by the virtual environment (VE) and intervention exercise will reduce the cognitive demands required to generate vivid future-oriented thought. Although we are not powered to assess this hypothesis in this pilot trial, we include the assessment measures to understand whether administration of these lengthier measures is feasible.

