## Methods/design

### Study design and timeline

The intervention is designed as a randomized, controlled, participant-blind, add-on superiority trial with three parallel groups. Block randomization will occur with a 1:1 allocation. All participants will receive a Coping Plan intervention [24]. Participants only randomized to receive the Coping Plan will constitute the TAU control group. The TAU control design was chosen to ensure ethical responsiveness to the needs of all participants. Participants in each of the two treatment arms will additionally receive the FutureU-MH intervention. As the intervention is administered via two sessions each targeting different elements of the future self, treatment groups will follow an AB/BA design to allow for differentiation of session effects.

Participants will be assessed at 5 time points: pre-intervention (prior to randomization and completion of the Coping Plan), post-Coping Plan, pre- and post- each intervention session, and at both 1-week and 3 months follow-up (see SPIRIT figure in Table 1). These methods were in accordance with the Declaration of Helsinki and approved by the Ethics Council of the Max-Planck Gesellschaft.

**Table 1 Tab1:** SPIRIT Figure for FutureU for Mental Health Trial

	Timepoint	− 1	0	t1	t2	**t3**	**f1**	**f2**	
Activity/assessment	Approx. time to complete	Screening and online consent	Baseline assessment	TAU: coping plan	Intervention P1 and pre-post assessments/or interim assessment 1 (Control)	Intervention P2 and pre-post assessments/or interim assessment 2 (Control)	1 week follow-up	3 month follow-up	End of study
Enrollment:									
Pre-screening consent	1 min	X							
Screening	3 min	X							
Informed consent (online)	10 min	X							
Random allocation	N/A		X						
Interventions:									
Coping plan intervention (TAU)	25 min			X					
Self-help intervention (in VR)	30 min				E *or*	E *or*			
Positive future memories intervention (in VR)	30 min				E	E			
Assessments:									
Demographics	5 min		X						
Beck Depression Inventory—II	10 min		X					X	
C-SSRS	5 min		X		X	X	X	X	
Self-efficacy	3 min		X					X	
Self-reported future self and mood	10 min		X		X	X	X	X	
Prospective imagery task	5 min		X					X	
BRIEF-A	15 min		X						
Engagement/embodiment	3 min				E	E			
Feasibility outcomes	N/A								X
Acceptability, feasibility, appropriateness	3 min				E	E			
Intervention use	1 min					E	E	E	

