### Interventions

Three interventions will be administered. First, as a treatment as usual control (TAU), a Coping Plan is administered by the experimenter during the first in-person session to all participants. Next, participants in the treatment condition (TX) will all receive the Self-Help Intervention (SH) and the Positive Future Memories Intervention (PFM)—collectively known as the FutureU for Mental Health (FU-MH) Intervention. Participants in the TX condition will be assigned to either group A or B, which will dictate the order in which the SH and PFM interventions are received. Group A will first receive SH and then PFM; Group B will first receive PFM and then SH.

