### Outcomes measures

All measures taken during in-lab sessions will be conducted on a laptop in the lab space. All measures taken during follow-up and online control sessions will be self-administered by participants via link to a Qualtrics survey.

*Primary objective measures—feasibility and acceptability of the intervention*
Feasibility: Number of eligible participants, willingness of participants to fully participate
(i)Rates of recruitment into the studyNumber of potentially eligible participants on SONA systems.Number of participants who completed the PHQ-9 screener and BDI-II item.Number (and proportion) of participants who were eligible to participate.Number (and proportion) of participants who were ineligible to participate at screening and why.Number (and proportion) of participants who consented to participate in intervention.Number (and proportion) of participants who scheduled the first in-lab session.Number (and proportion) of participants who completed the first in-lab session.(ii)Retention to treatmentNumber (and proportion) of participants who successfully completed all parts of the intervention (sessions 1, 2, and 3).Number (and proportion) of participants who drop out of the study and, when freely shared, reasons for drop out. In accordance with our informed consent, participants are free to drop out of the study at any point without explanation.(iii)Completion of between session tasks(iv)Number (and proportion) of participants who report needing to use their Coping Plan.(v)Number (and proportion) of participants who report using their Coping Plan when needed.(vi)Number (and proportion) of participants who report listening to their Self-Help recording in the week following the intervention session and 3 months following the intervention session.(vii)Number (and proportion) of participants who report listening to their Positive Future Memories recording in the week following the intervention session and 3 months following the intervention session.(viii)Attrition at post-treatment follow-up pointsNumber (and proportion) of participants who complete the 1-week follow-up questionnaire.Number (and proportion) of participants who complete the 1-month follow-up questionnaire.(ix)Levels of missing clinical outcome dataProportion of data completion for each questionnaire at each time-point.

Feasibility: Adherence/Compliance rates—Rating and adherence to intervention protocol. See above for details.

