(i)Improvement in symptoms of depression—Participants will respond to the Beck Depression Inventory—II (BDI-II) at baseline and at the 3-month follow-up session [48]. The BDI-II is the most widely used measure of depressive symptoms and has demonstrated good reliability and validity in clinical and nonclinical German samples [49]. The scale is comprised of 21 items assessing the presence and severity of depressive symptoms. Each item includes 4 response options ranging from no experience of symptoms to severe experience of symptoms; for example, 0 – *I do not feel sad* to 3 – *I am so sad or unhappy that I can’t stand it*. Scores are obtained by summing total items and range from 0 to 63. Total scores from 0 to 13 indicate minimal depression, 14 to 19 mild depression, 20 to 28 moderate depression, and 29 to 63 severe depression.Improvement in reported symptoms of depression among participants in the treatment condition from baseline to 3-months post-intervention follow-up.A larger improvement in reported symptoms of depression among participants in the treatment condition versus participants in the control condition from baseline to 3-months follow-up.(ii)Reduction in frequency and severity of suicidal ideation – Participants will respond to the German language validated Columbia – Suicide Severity Rating Scale adapted for use in Research [50] at baseline, each pre-intervention questionnaire, and the 1-week and 3-month follow-up. Based on responses, participant scores will be categorized as low, moderate, or high risk.Improvement in reported frequency and severity of suicidal ideation among participants in the treatment condition from baseline to each measurement occurring post-intervention (i.e., session 3 pre-intervention, 1-week follow up, 3-month follow up).A larger improvement in reported frequency and severity of suicidal ideation among participants in the treatment condition versus participants in the control condition from baseline to each measurement occurring post-intervention (i.e., session 3 pre-intervention, 1-week follow up, 3-month follow up).(iii)Reduction of negative affect, Improvement in Positive Affect—Participants will respond to the German language validated Positive and Negative Affect Scale (PANAS) at every measurement point [51]. The PANAS is made up of two 10-item scales measuring positive and negative affect. Each item is rated on a scale from 1 = Very Slightly, or Not at all to 5 = Extremely. Scores are obtained by averaging responses to items within the positive and negative subscales.Improvement in affect, i.e., increase in positive affect and decrease in negative affect, among participants in the treatment group from pre-to-post intervention and from baseline to 1-week and 3-month follow-up.A larger improvement in affect among participants in the treatment condition versus participants in the control condition from baseline to each measurement occurring post-intervention.(iv)Improvement in self-efficacy—Participants will respond to the German language validated General Self Efficacy Scale (GSES) at baseline and 3-month follow-up [52]. The scale has 10 items assessing participants’ overall sense of self-efficacy with dealing with difficulties. Items are rated on a scale from 1 = Completely Disagree to 4 = Completely Agree. Scores are obtained by averaging scores across all items.Improvement in self-efficacy among participants in the treatment condition from baseline to 3-month follow-up.A larger improvement in self-efficacy among participants in the treatment condition versus participants in the control condition from baseline to 3-month follow-up.

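### The C-SSRS item counts the rating before session 3 as post-intervention, although nobody has then had both VR parts; it should be labelled interim (after part 1) and reported by order group

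*Protocol article*

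**What the plan says.** The section on outcome measures in the protocol article schedules the C-SSRS "at baseline, each pre-intervention questionnaire, and the 1-week and 3-month follow-up". It then makes two effect statements, one for improvement within the treatment condition and one for treatment against control. Both run from baseline to "each measurement occurring post-intervention (i.e., session 3 pre-intervention, 1-week follow up, 3-month follow up".

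Elsewhere the article fixes what the intervention is and when its effect is judged:

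- Under Interventions, the two VR parts are "collectively known as the FutureU for Mental Health (FU-MH) Intervention", and their order differs by arm: "Group A will first receive SH and then PFM; Group B will first receive PFM and then SH".
- Under Research hypotheses, the efficacy hypothesis is for the "Coping Plan plus Self-Help and Positive Future Memories interventions, collectively".
- Under Secondary objectives, clinical improvement against control is to be shown "both immediately following the intervention, and 1 week and 3 months post intervention".
- Table 1 places "Intervention P2 and pre-post assessments/or interim assessment 2 (Control" at t3, and the retention outcome counts participants who "successfully completed all parts of the intervention (sessions 1, 2, and 3".
- Under Study design and timeline, the AB/BA arrangement is justified as a way of telling the effects of the two sessions apart.

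**The concern.** The C-SSRS item gives a closed list, and its first entry precedes the second VR part. On the article's own definition of FU-MH, that rating comes before anyone has completed the intervention. Even so, it is listed on the same footing as the 1-week and 3-month ratings and for a single pooled treatment condition.

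Two things are at stake. First, a result at that time point could be credited to, or counted against, a package that no participant had yet received in full. Second, this is the only C-SSRS rating at which Groups A and B differ in which VR part they have had. Pooling the arms there sets aside the comparison for which the two orders were introduced.

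**Working it through.** The protocol states no effect size, significance level or power for the C-SSRS, so there is no figure to reproduce. The check rests on the visit schedule.

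**Inputs.** The order of parts by group is from Interventions. The session at which each part is given is from Table 1. The C-SSRS rating times are from the outcomes section. The planned 20 per group is from the progression criteria (Table 2).

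**VR parts received before each C-SSRS rating**

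| Rating | Group A (20) | Group B (20) | Control (20) | Treated with both parts |
|---|---|---|---|---|
| Session 2, pre | none | none | none | 0 of 40 |
| Session 3, pre | Self-Help | Positive Future Memories | none | 0 of 40 |
| 1 week | both | both | none | 40 of 40 |
| 3 months | both | both | none | 40 of 40 |

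The table assumes full attendance at the planned sample size.

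**Reading across**

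1. At session 3 pre-intervention the treatment condition is a 20/20 mixture of two different single-part exposures. From 1 week onward the two arms have had the same content in different order.
2. The list has 3 time points and appears in 2 effect statements, giving 3 × 2 = 6 contrasts. The session 3 entry accounts for 1 × 2 = 2 of them. The other 4 follow the full intervention.
3. The secondary objective names three occasions: immediately after, 1 week after and 3 months after the intervention. The C-SSRS is not scheduled after the second VR part within session 3, so it has no rating at the first occasion. The session 3 pre-intervention rating cannot stand in for it, because it falls on the other side of the second part.

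**Precision of reporting by order.** With a common standard deviation σ, the standard error of a difference in means is σ√(1/n₁ + 1/n₂).

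- Pooled, 40 versus 20: σ√(1/40 + 1/20) = σ√0.075 = 0.274σ.
- By order, 20 versus 20: σ√(1/20 + 1/20) = σ√0.100 = 0.316σ.
- Ratio: √(0.100/0.075) = 1.155.

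Each by-order contrast therefore has a standard error about 15% larger than the pooled one. This is a rough guide only, because the article also sorts C-SSRS responses into three risk categories.

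**The case against.** The strongest reply is that the article also uses the word intervention for each VR session. The C-SSRS item itself speaks of more than one pre-intervention questionnaire, the Interventions section says three interventions are administered, and Table 1 has separate columns for P1 and P2. In that usage the session 3 pre-intervention rating is simply the first after any VR exposure, and the session 2 rating is correctly left out. The time point is named in full, so nobody is misled about when the measurement was taken.

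Much of this stands: the wording is open, and the authors may well have meant after the first VR session. It does not remove the point. The hypothesis is still stated for the parts collectively, and on the per-session reading the contrast still pools two different exposures at the one C-SSRS rating where they could be compared.

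Other parts of the reply limit how far the point goes:

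- A reader might infer that a weak result at this rating would be taken as failure of the whole intervention. The article does not support that. Research hypotheses expects the strongest effects at the two follow-ups, and the analysis section expects growth over time and fits a growth model to examine it.
- A reader might infer that the contrast carries exactly half the full effect, with a calculable loss of power. That needs additive parts, no change of effect with time and a continuous score. The article gives no basis for the first, expects growth instead of the second, and categorises the C-SSRS. No power figure belongs here.
- A reader might infer the same fault in the future-self measures and the PANAS. Their effect statements refer to post-intervention measurements without a list that includes session 3 pre-intervention, so no error is shown there.
- Reporting by order is not ruled out anywhere, and detailed tabulation may sit in a fuller document. The point concerns the explicit list, not missing detail.

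**Conclusion.** The point holds as a minor one. Twice, the C-SSRS item labels as post-intervention a rating that comes before any participant has had both VR parts. This affects 1 of 3 time points, or 2 of 6 listed contrasts; the 1-week and 3-month contrasts are sound.

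The conclusion rests on the visit schedule and on taking FU-MH as the two VR parts together, as Interventions defines it. It does not mean that treated participants have had nothing by then: all participants, controls included, are planned to have had the Coping Plan, which the introduction to FU-MH counts as a third part.

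The consequence is modest. The outcome is secondary, the article describes these analyses as exploratory and the trial as not powered for clinical outcomes, and no progression criterion depends on the C-SSRS. The rating itself is legitimate and useful. What needs correcting is its label and the pooling across orders.

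**What to change.** For the C-SSRS item only:

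1. Take the session 3 pre-intervention rating out of the post-intervention list in both effect statements and name it an interim (after part 1) rating.
2. Report it by order group: Group A against control for Self-Help alone, and Group B against control for Positive Future Memories alone.
3. State that the 1-week and 3-month ratings are the contrasts bearing on the full FU-MH intervention.
4. Keep the interim rating in the trajectory model, where an intermediate observation is informative.

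Do not carry a rule restricted to 1 week and 3 months over to the future-self measures or the PANAS. Both are scheduled at t3 with pre-post assessments, and the session 3 post rating follows both parts. Any shared definition must keep that rating as the occasion immediately after the intervention, which the secondary objective requires.

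The change is to wording and reporting and needs no new data. One fewer C-SSRS time point counts as evidence for the full package, and each by-order contrast is less precise than the pooled one.

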
#### Continued development of intervention procedure and protocol

In both parts of the intervention, audio recordings will be taken of the intervention targets, i.e., coping statements in SH and positive future memory in PFM. These recordings will be used post-completion of the trial to evaluate and improve the intervention procedure and protocol.

### Analyses

#### Primary objective—feasibility and acceptability of the intervention

As outlined in the outcomes section, descriptive data on the feasibility and acceptability of the intervention will be provided. Descriptive statistics will be reported for continuous and pseudo-continuous variables assessing each individual part of the intervention, i.e., for the SH and PFM interventions. Frequencies will be reported for categorical data.

Participant’s progress through the trial will be reported in a CONSORT diagram*—*see Fig. 7. This will indicate the number of participants who were eligible, consented, began, and completed the study, as well as the number of participants who dropped out, at which timepoint, and why (if reason is known).

**Fig. 7 Fig7:**
[figure not shown]
CONSORT Flow Diagram for FutureU for Mental Health Trial

#### Secondary objective—establishing a proof of concept for the intervention

Assessment of change in targeted cognitive mechanisms and clinical outcomes will be completed as is outlined in the outcomes section. Due to the modest sample size, these analyses will be completed to pilot the method for a full-scale RCT and to explore trends. The significance of effects will be interpreted and discussed within the context of the statistical limitations of a pilot trial.

Between-group differences for participants in the treatment condition versus the control condition will be assessed using independent-sample *t*-tests. Here, interpretation of Cohen’s *d *will be done using between-group standard deviations. The significance of between-subject changes will also be assessed through calculation of a reliable change index (RCI) [53] and evaluation of confidence intervals for mean differences.

Between-group differences in the targeted cognitive mechanisms and clinical outcomes will additionally be assessed through Latent Growth Curve Modeling (LGCM). This analysis will allow us to evaluate the difference in trajectories of change in cognitive mechanisms and clinical outcomes between the control and treatment conditions. The hypothesized changes in thought processes and subsequent clinical outcomes are expected to continue to grow over time post-intervention, rather than improve wholly and discretely at the point of intervention. The LGCM approach will allow us to observe whether this growth hypothesis is borne out.

For all analyses, age and gender will be included as covariates. Gender is included for the potential biasing effect on reports of depression. Cross-nationally, women endorse depression at highly elevated rates versus men [54]. Age is included for the potential biasing effects on future-oriented thinking. The future is conceived differently at different stages of life. Although variation in stages of life is comparatively low given the already constricted age range (18–24), there are still some meaningful differences in life stage that may impact future perspective when comparing an 18 versus 24-year-old.

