Valence:Improvement in the valence of thoughts of the future self (i.e., thoughts becoming more positive) among participants in the treatment condition from pre-to-post intervention.A larger improvement in the valence of thoughts of the future self among participants in the treatment condition versus participants in the control condition from baseline to each measurement point post-intervention.VividnessImprovement in the vividness of thoughts of the future self (i.e., the mental image becoming clearer and more detailed) among participants in the treatment condition from pre-to-post intervention.A larger improvement in the vividness of thoughts of the future self among participants in the treatment condition versus participants in the control condition from baseline to each measurement point post-intervention.RelatednessImprovement in the sense of connection to the future self among participants in the treatment condition from pre-to-post intervention.A larger improvement in the sense of connection to the future self among participants in the treatment condition versus participants in the control condition from baseline to each measurement point post-intervention.Improvement in the sense of similarity to the future self among participants in the treatment condition from pre-to-post intervention.A larger improvement in the sense of similarity to the future self among participants in the treatment condition versus participants in the control condition from baseline to each measurement point post-intervention.
(ii)Improvement in quality of future thoughts—Participants will complete the Prospective Imagery Task (PIT) at the baseline and final assessments [47]. The PIT asks participants to generate a mental image in response to 10 negative future scenarios and 10 positive future scenarios and indicate how vivid each image is on a scale from 1 = no image at all to 5 = very vivid.Improvement in the vividness of future thoughts among participants in the treatment condition from baseline to 3-months post-intervention follow-up.A larger improvement in the vividness of future thoughts among participants in the treatment condition versus participants in the control condition from baseline to 3-months follow-up.

*Demonstrating evidence of improvement in clinical outcomes*

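### Growth curves are assigned to every mechanism and clinical outcome, but the BDI-II, PIT and GSES are measured only at baseline and 3 months, so post-intervention growth cannot be tested for these three scales

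*Protocol article*

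**What the plan says.** In the Protocol article, under Analyses (Secondary objective), the between-group comparison is made first by independent-sample t-tests with Cohen's d, a reliable change index and confidence intervals for mean differences. A second method follows: "Between-group differences in the targeted cognitive mechanisms and clinical outcomes will additionally be assessed through Latent Growth Curve Modeling (LGCM"). Its purpose is stated. Changes in thought processes and clinical outcomes "are expected to continue to grow over time post-intervention, rather than improve wholly and discretely at the point of intervention", and "The LGCM approach will allow us to observe whether this growth hypothesis is borne out". Research hypotheses names depressive symptoms among the effects expected to grow and adds that "These effects will be strongest at the 1-week and 3-month follow-ups".

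The measurement schedule is in Outcomes measures and Table 1:

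- Depression: "Participants will respond to the Beck Depression Inventory—II (BDI-II) at baseline and at the 3-month follow-up session".
- Vividness of future thoughts: "Participants will complete the Prospective Imagery Task (PIT) at the baseline and final assessments".
- Self-efficacy: "General Self Efficacy Scale (GSES) at baseline and 3-month follow-up".
- Suicidal ideation, for comparison, is assessed "at baseline, each pre-intervention questionnaire, and the 1-week and 3-month follow-up".

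The BDI-II and GSES are listed as clinical outcomes and the PIT as a cognitive mechanism, so all three fall within the stated scope of the growth model.

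**The concern.** The article promises a test of the shape of change for outcomes whose schedule cannot reveal shape. Depression matters most here. The PHQ-9 is used only at screening, so the BDI-II carries all the post-baseline information on depressive symptoms, and it has a single post-intervention value. It is not collected at the 1-week follow-up, one of the two times at which the effect is expected to be strongest.

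If the analysis were run as written, it would either fail to estimate or be forced through by fixing variances. In the second case a plain baseline-to-3-month difference would be printed as a slope and could be reported as evidence of continued growth. The article says these analyses serve to pilot the method for a full-scale trial, so the mismatch could carry over into that trial's schedule and analysis.

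**Working it through.** The plan gives no figure to reproduce here. The check counts waves per outcome and then asks what a growth model can identify.

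**1. Waves per outcome** (Table 1 and Outcomes measures)

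| Outcome | Waves | Values after the last session |
|---|---|---|
| BDI-II | 2 (baseline, 3 months) | 1 |
| PIT | 2 (baseline, 3 months) | 1 |
| GSES | 2 (baseline, 3 months) | 1 |
| C-SSRS | 5 (baseline, t2, t3, 1 week, 3 months) | 2 |
| Future-self measures | at least 5 | 2 |
| PANAS | at least 5 (every measurement point) | 2 |

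**2. Shape from two points.** Let the baseline mean be b and the total change by 3 months be d. If all of d occurs at the sessions and is then held, the observed pair is (b, b + d). If d accrues gradually up to 3 months, the observed pair is again (b, b + d). The data are the same, so no model can separate the two accounts. This holds whatever growth specification is chosen.

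**3. Identification of the standard linear model.** With T waves, the observed means, variances and covariances number T(T + 3)/2. The free parameters are 2 factor means, 2 factor variances and 1 factor covariance, plus T residual variances (free) or 1 (held equal).

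- T = 2: moments = 2 × 5/2 = 5.
  - Free residuals: 5 + 2 = 7 parameters, df = 5 - 7 = -2.
  - Equal residuals: 5 + 1 = 6 parameters, df = 5 - 6 = -1.
  - A numerical Jacobian has rank 5 in both cases, so neither is identified.
- T = 3, free residuals: 9 moments, 8 parameters, df = 1, rank 8 (identified).
- T = 5, free residuals: 20 moments, 10 parameters, df = 10, rank 10 (identified).

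**4. Covariates do not help.** Group, age and gender add 3T = 6 moments at T = 2 and 6 paths (three each to intercept and slope). Then df = 11 - 13 = -2 or 11 - 12 = -1, as before.

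**5. Constrained two-wave versions.**

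- Residual variances fixed at zero: 5 parameters, df = 0. The slope is then the observed change score.
- Slope variance (and its covariance) fixed at zero, equal residuals: 2 means + intercept variance + residual variance = 4 parameters, df = 1. With free residuals: 5 parameters, df = 0.

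These can be fitted. With complete data, the arm effect on the slope is the between-arm difference in mean change from baseline to 3 months, which the simpler planned comparison already gives.

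**The case against.** The strongest reply is that little is lost. Growth modelling is an additional analysis. For the BDI-II, PIT and GSES the outcomes section sets its targets as change from baseline to 3 months, within the treatment condition and against control, and two waves are enough for that. A reader might infer that depression is left without any valid analysis. The article does not support this, because the t-tests, reliable change index and confidence intervals still apply.

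Second, the negative degrees of freedom depend on a specification that the article does not give. That is correct, and step 5 shows identified alternatives. They rescue the mean contrast only. Step 2, which carries the finding, assumes no particular model.

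Third, a reader might extend the criticism to the five-wave outcomes, arguing that one slope from baseline would mix change during the sessions with change after them. The article nowhere commits to a single linear slope. A growth model may be piecewise, and functional form is ordinarily left to the analysis plan, so this is not a defect of the document.

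Fourth, the analyses are exploratory, and progression rests on feasibility and acceptability alone. That stands and lowers the grade. It does not remove the contradiction, since no analysis plan could recover shape from two waves; it could only narrow a scope that the article states without exception.

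Finally, the attrition list mentions a 1-month follow-up questionnaire. Neither Table 1 nor any outcome description schedules a scale then, so it cannot be counted as a third wave.

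**Conclusion.** The point holds for three scales. For the BDI-II, PIT and GSES the growth hypothesis cannot be tested on the planned schedule. The usual random-intercept, random-slope model falls short by 1 or 2 degrees of freedom, and the versions that can be fitted return only the mean-change contrast. The growth claim is therefore unsupported for depression, prospective imagery and self-efficacy, whatever the sample size.

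The severity is moderate. The baseline-to-3-month comparison survives, the outcomes are secondary, and no progression decision depends on them. It would be too strong to say that the proof of concept fails: that objective can also be met through negative affect, and the PANAS, the future-self measures and the C-SSRS have enough waves for a growth analysis in principle. The conclusion assumes that the schedule in Table 1 is complete for the three scales; the outcome descriptions agree with it.

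**What to change.** Change the analysis text in three places.

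1. Restrict latent growth curve modelling, and the statement that it will test continued growth, to outcomes with at least three waves: the PANAS, the future-self measures and the C-SSRS. Because the C-SSRS is to be categorised as low, moderate or high risk, name a model suited to ordered categories for it.
2. For the BDI-II, PIT and GSES, compare the arms at 3 months by a regression adjusted for the baseline value, age and gender, and state that no growth claim will be made. Age and gender are already required as covariates in all analyses. A comparison of change scores would also cure the mismatch; baseline adjustment is the recommended form.
3. For the multi-wave outcomes, state that post-intervention growth is tested as the between-arm difference in change from the 1-week to the 3-month follow-up.

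The cost is wording only, with no new data collection. The growth claim is given up for three scales, including the depression scale. If the full-scale trial is meant to test growth in depressive symptoms, its schedule will need more than one post-intervention BDI-II, and the pilot report should say so.
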